# STUDY BACKGROUND INFORMATION AND RATIONALE

## BACKGROUND

Immune checkpoint inhibitors (CPIs) have evolved over the last decade and treatment with a single CPI or a combination of CPIs has extended survival of patients with a variety of epithelial and lymphoid malignancies. The three major targets of CPIs are cytotoxic T-lymphocyte-associated antigen 4 (CTLA-4), programmed cell death protein 1 (PD-1), and its ligand, programmed cell death ligand 1 (PD-L1). They work by blocking immune suppressive ligand-receptor interactions which enhances the anticancer cytotoxic effects of lymphocytes. However, because checkpoint molecules are also involved in immune tolerance, unfavourable reactions to self-antigens potentially occur [1]. CPIs are associated with immune-related adverse events (irAE) in multiple organ systems including liver. Immune-mediated hepatitis is frequently observed in cancer patients treated with CPIs, up to 5% in single agent or 18% in combination therapies [2]. Checkpoint inhibitor-induced liver injury (ChILI) usually develops many weeks or even months after the start of the therapy, thus an early diagnosis of checkpoint inhibitor-induced hepatitis would help guide cancer therapy and management of drug-induced liver injury (DILI).

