## RATIONALE FOR CURRENT STUDY:

Despite remarkable progress in the treatment of several advanced malignancies with CPIs, immune mediated adverse events including checkpoint inhibitor-induced liver injury have been a real clinical challenge not only for physicians but also for cancer patients. This is due to the unpredictable nature of liver injury, lack of robust evidence to guide management and the potential consequences of stopping checkpoint inhibitor treatment. Current guidelines (European Society of Medical Oncology) suggest grading of the liver injury based on liver biochemistry test results: grade 1: alanine transaminase (ALT) or aspartate aminotransferase (AST) > 1 to 3 times upper limit of normal (ULN), grade 2 = ALT or AST >3 to 5 ULN, grade 3 = ALT or AST > 5 to 20 ULN and grade 4 = ALT or AST > 20 ULN [3]

Treatment guidelines for checkpoint inhibitor-induced liver injury are based on colitis and auto-immune hepatitis models with high dose corticosteroids being recommended for grade 3-4 liver injury or persistent grade 2 liver injury [3, 4]. However, steroids in cancer patients can cause serious adverse events and recent reports suggest that around 35% of grade 3/4 hepatitis regresses spontaneously without intervention [5, 6].

The immune-mediated liver injury induced by checkpoint inhibitors is much more frequent, a new and incompletely understood category of hepatotoxicity and distinct from other types of drug induced liver injury (DILI) such as direct or idiosyncratic DILI. Recent evidence suggests that ChILI is primarily mediated by CD8+ T cells, and it is associated with increased T cell activation and infiltration in the liver and with a characteristic histopathologic feature of necrotic/degenerative hepatocytes surrounded by ring-like T cell clusters [7]. This is different from direct chemically-induced, hepatocyte-intrinsic cell damage and death where hepatocyte cell death is typically the primary initiator of the inflammatory response [8]. This histologic feature is also different from autoimmune hepatitis or idiosyncratic DILI in humans [9].

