## SECONDARY OBJECTIVES

1. To study the natural history of patients treated with checkpoint inhibitors after developing ChILI.
2. To identify specific phenotypic features associated with ChILI compared to idiopathic auto-immune hepatitis and DILI due to other drugs. This includes histological characteristics, genetic, biochemical and immunological characteristics.
3. To determine association between biomarkers, clinical features and development of ChILI.

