#### Part 1. CPI cohort study (before & after CPI therapy)

We will prospectively develop a cohort of oncology patients (**cohort study**), with malignant melanoma, renal cell carcinoma, non-small cell lung cancer or any other cancer, receiving single or combination therapy using checkpoint inhibitors (CPIs). Two visits will be undertaken (prior starting CPI therapy and 6-14 weeks after treatment, when collection and storage of biological samples and data (medical, demographic and clinical) will be obtained. Timing of ChILI ranges from 1 – 49 weeks following treatment with a peak around 6 – 14 weeks [5] ,

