### Part 3. Cross-sectional case/control study (comparing patients in parts 1 and 2)

We will run a cross-sectional case control study comparing biological samples of patients in the cohort study who did not develop ChILI after 6-14 weeks of CPI treatment (controls) with patients in the second study who developed ChILI (cases). A small percentage of patients in the cohort study (3-18%) will develop ChILI and will be added to the cases; they will have 4 visits in total (one prior CPI treatment and 3 visits following reaction). We will compare samples from visit 2 in controls (after 6-14 weeks of treatment without developing ChILI) and visit 1 in cases (time of reaction).

[figure not shown]

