#### Control Group:

Consecutive patients with cancer who have clinical indication to start checkpoint inhibitors will be approached for consent to be enrolled in the study. We will enrol 120 consecutive patients who will be identified as controls. A small proportion of patients will develop ChILI following their checkpoint inhibitor treatment and will be classified as cases.

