## STATISTICS

### Statistical analysis

- We will calculate the incidence of ChILI and other irAE in the cohort group.
- We will describe demographic and clinical data for the enrolled participants using descriptive statistics, mean  $\pm$  standard deviation (SD) for continuous measurements and frequencies and percentiles for categorical data. We will compare patients' pathological and clinical characteristics using Chi-square test for categorical variables and Wilcoxon/Kruskal-Wallis test for the continuous variables.  $P < 0.05$  will be considered statistically significant.
- We will assess the accuracy of the biomarkers for ChILI detection and predicting prognosis using receiver operating characteristic (ROC) curve and the area under the ROC curve (AUC) with 95% confidence interval (CI).
- We will assess the correlation of biomarkers with ALT using Pearson's  $r$  coefficient.

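### Part 3 compares unmatched cases and controls with unadjusted analyses, although the protocol's own rates imply different CPI regimens in the two groups, so a marker of combination therapy can be reported as a ChILI marker

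*Protocol*

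**What the plan says.** Part 3 of the protocol fixes the contrast: "We will compare samples from visit 2 in controls (after 6-14 weeks of treatment without developing ChILI) and visit 1 in cases", the case visit being the time of reaction. Part 1 gives the case timing: "Timing of ChILI ranges from 1 – 49 weeks following treatment with a peak around 6 – 14 weeks". Single-agent and combination CPI are both allowed, in the cohort (Part 1) and among ChILI patients (Eligibility criteria).

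Controls are not matched. Under Control Group: "Consecutive patients with cancer who have clinical indication to start checkpoint inhibitors will be approached for consent". The Background puts immune-mediated hepatitis at "up to 5% in single agent or 18% in combination therapies".

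Statistical analysis assigns biomarkers to ROC curves with AUC and 95% confidence interval, and to Pearson's r against ALT. Pathological and clinical characteristics are compared "using Chi-square test for categorical variables and Wilcoxon/Kruskal-Wallis test for the continuous variables", at P < 0.05. No covariate, stratum or matching factor is named anywhere.

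On steroids, the Rationale reports "high dose corticosteroids being recommended for grade 3-4 liver injury". Study Treatment and Regimen allows up to two weeks between identification of an episode and consent. The exclusion criteria do not mention steroids. Appendix 1 schedules the six-month drug history at visit 1 only, which for controls is before CPI.

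Secondary objective 3 is "To determine association between biomarkers, clinical features and development of ChILI".

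**The concern.** The Rationale argues that candidate immune markers reflect CPI pharmacology, and that immune-related adverse events arise through the same pharmacology. A marker of heavier CPI exposure is therefore what this contrast could mistake for a marker of liver injury. If combination therapy is more common among cases, an unadjusted AUC mixes the two.

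Time on CPI also differs: cases may be sampled at any point in weeks 1-49, controls only in weeks 6-14. Some cases may have started steroids before their sample.

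At stake are primary outcome 2 (biomarkers associated with the diagnosis of ChILI) and the secondary risk-factor outcome. In addition, the only sample contrast specified is taken after injury, so it cannot by itself address the development of ChILI in secondary objective 3.

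**Working it through.** **Plan's own figure.** The 40 cases and 120 controls are justified by feasibility; no power, effect size or SD is given, so there is nothing to reproduce.

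**Inputs from the protocol.** ChILI rate 5% (single agent) and 18% (combination), both read from an up-to statement; 40 cases, 120 controls; significance at 0.05 (two-sided assumed).

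**Assumed, not in the protocol.** Share c of treated patients on combination, 10-70%; marker shift due to combination, 0.5 or 1 SD; one source population for cases and controls.

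**Step 1, odds ratio.** (0.18/0.82) / (0.05/0.95) = 4.17, whatever the value of c.

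**Step 2, regimen mix.** Cases on combination = 0.18c / [0.18c + 0.05(1 − c)]; controls = 0.82c / [0.82c + 0.95(1 − c)]. At c = 0.30: cases 0.054/0.089 = 0.607; controls 0.246/0.911 = 0.270.

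**Step 3, a marker that only records regimen.** AUC = 0.5 + (cases − controls)/2. At c = 0.30: 0.5 + (0.607 − 0.270)/2 = 0.668. Over c = 10-70%, a two-proportion comparison at 40 v 120 would be significant with probability 84-97%.

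**Step 4, a continuous marker unrelated to ChILI within regimen.** Normal marker, shifted only by combination; 3,000 simulated studies per cell; Wilcoxon test at 0.05, then a linear model with regimen as covariate. The Wilcoxon statistic divided by 40 × 120 = 4,800 is the AUC, so the rank test closely tracks whether the planned 95% interval for the AUC excludes 0.5.

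| c | Cases / controls on combination | AUC, regimen-only marker | Unadjusted P<0.05: 0.5 SD / 1 SD | Mean AUC: 0.5 SD / 1 SD | Regimen-adjusted P<0.05: 0.5 SD / 1 SD |
|---|---|---|---|---|---|
| 10% | 29% / 9% | 0.60 | 8% / 16% | 0.53 / 0.55 | 4.9% / 4.6% |
| 20% | 47% / 18% | 0.65 | 13% / 30% | 0.54 / 0.58 | 5.2% / 5.2% |
| 30% | 61% / 27% | 0.67 | 16% / 39% | 0.55 / 0.59 | 5.2% / 5.6% |
| 50% | 78% / 46% | 0.66 | 13% / 35% | 0.54 / 0.58 | 4.7% / 4.6% |
| 70% | 89% / 67% | 0.61 | 9% / 21% | 0.53 / 0.56 | 4.9% / 5.4% |

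With no shift the unadjusted test gives 5.6%, near nominal. Simulation error is at most about 2 percentage points.

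**Step 5, time on CPI (illustration only).** Assume log-normal onset with median 9 or 12 weeks and log-SD 0.8, limited to weeks 1-49; controls uniform over weeks 6-14; drift of 0.5-1 SD per 10 weeks. False positives are 8-48%, and 59-62% of cases fall outside weeks 6-14. These figures depend heavily on the assumed onset distribution.

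**Step 6, steroids (illustration only).** If 10-75% of cases and no controls were exposed, false positives would be 5-51% at a 0.5 SD shift and 8-97% at 1 SD. The range is this wide because the protocol gives no exposure figure.

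**Step 7, cases with a pre-CPI sample.** With 120 cohort patients and the 3-18% stated in Part 3: 120 × 0.03 = 3.6 and 120 × 0.18 = 21.6, so about 4-22.

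**The case against.** **A statistical analysis plan may add covariates.** One may exist, and the Rationale does speak of algorithms that use CPI-related factors. This lowers the severity. It does not remove the point, because the protocol itself fixes the unmatched contrast, lists only unadjusted methods and sets the data-collection schedule.

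**The Wilcoxon sentence concerns clinical characteristics, not biomarkers.** Correct. The biomarker analysis is ROC/AUC, but that is unadjusted too, and the rank-test rates carry over as noted in step 4. The mean AUCs of 0.53-0.59 are modest; 0.60-0.67 needs a marker that records regimen perfectly.

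**The control window was chosen to match the peak of onset.** This stands: only the tails of case timing differ.

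**The study is mechanistic, not an evaluation of biomarker performance** (Sample size and justification). This also lowers severity, yet biomarker identification is a primary outcome and AUCs for detection are planned.

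**Stronger readings a reader might infer.**
- That regimen markers will be reported as ChILI markers. The documents support only that they can be: marker shifts and regimen mix are not given, the 5% and 18% are upper figures for hepatitis rather than rates at this study's thresholds, and Part 2 cases are recruited separately.
- That cases are often sampled after steroids. No frequency is given. Two weeks is a maximum lag, bloods must still meet the thresholds on the enrolment day, the Rationale describes guidelines rather than practice in this study, and controls may receive steroids for other reactions.
- That the primary biomarker aim claims prediction of onset. It does not: Proposal Aims and Primary Outcome Measure are already limited to diagnosis.

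**Conclusion.** The point holds as a should-fix. Followed as written, Part 3 can attribute to ChILI what belongs to combination therapy. The odds ratio of about 4.2 follows from the protocol's two rates taken at face value. The consequences for AUC and false positives (0.53-0.67 and about 8-39%) rest on an assumed 10-70% combination share and, for the continuous marker, an assumed 0.5-1 SD shift; adjusting for regimen returns the error rate to about 5%.

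The difference in time on CPI is real but confined to onset outside weeks 6-14. Steroid exposure before the case sample is possible, and its extent is unknown. The gap on development of ChILI affects the secondary objective only: pre-CPI samples are collected, but no comparison is specified for them.

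**What to change.** In Part 3 and Statistical analysis:

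1. Make a regimen-stratified or regimen-adjusted analysis the main one for Part 3 and the risk-factor comparison: stratified or covariate-adjusted AUC, van Elteren test, or penalised logistic regression. In the risk-factor model, report regimen as a factor in its own right. Forty cases support only a few covariates.
2. Handle time on CPI mainly by a sensitivity analysis limited to cases sampled in weeks 6-14. Model adjustment for weeks would extrapolate, since no control is sampled outside that window.
3. In Appendix 1, record steroid exposure at every sampling visit, including control visit 2, and add a sensitivity analysis in cases sampled before any steroid.
4. State that the at-reaction contrast supports claims about diagnosis only. For development of ChILI, add a comparison, nested in Part 1, of pre-CPI samples from patients who do and do not develop it, labelled exploratory.

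**Cost.** Protocol wording and one added CRF item. Regimen should already be available from the pharmacological history, though the CRF is not shown and this should be confirmed. Intervals widen slightly. Under the step 5 assumptions the weeks 6-14 analysis keeps only about 40% of cases (40 × 0.40 = 16), and the nested comparison has about 4-22 cases, so both support the main analysis rather than replace it.

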### Part 4. Liver Histology Study

We aim to compare histological characteristics of ChILI with idiopathic autoimmune hepatitis (AIH) and DILI due to other drugs. We expect to obtain 10 liver biopsies from patients with ChILI and perform histological comparison with up to 25 liver biopsies of DILI and 50 biopsies of auto-immune hepatitis available retrospectively and prospectively through other REC/HRA-approved research studies (where consent is given for researchers to access surplus diagnostic material) and requested from research tissue banks (such as NDDC BRU Research tissue bank REC Ref 19/WA/0288 IRAS 269958 and Transbioline Prospective European drug-induced liver injury registry (PRO-EURO DILI) REC 15/YH/0294 (based within the University of Nottingham).

In order to obtain sufficient samples which meet histopathologist-confirmed disease definitions, we will also request surplus FFPE tissue, remaining in archives after clinical diagnosis, from the pathology department at Nottingham University Hospitals NHS Trust. (NUHT) Samples relating to cases coded as confirmed DILI or AIH in medical notes will be, randomly selected and released in fully anonymised

format (with no associated personal data) by the clinical pathology translational research team to the study research team. We will also approach other research tissue banks (e.g. Birmingham or Liverpool) to request further tissue samples required if necessary to complete the study since samples available may be limited. Samples will be FFPE-preserved liver tissue for histology analysis by pathologist and material for phenotypic analysis (e.g. histochemical or genetic/expression). Fresh-frozen liver tissue samples will also be analysed where available. This will enable us to develop a clear picture of cellular changes in the liver associated with the natural history of ChILI.

### **NHS secondary care hospital sites in the UK (Including Scotland)**

#### **Primary endpoint**

Following acquisition of clinical samples and collation of associated comprehensive demographic, phenotypic and clinical data collected from a total of: 40 patients who develop checkpoint inhibitors-induced liver injury (ChILI) and 120 patients with cancer are treated with checkpoint inhibitors, we aim to:

1. Measure the incidence of liver injury secondary to checkpoint inhibitors and other adverse events.
2. Identify and characterise biomarkers associated with ChILI.

#### **Secondary endpoint**

1. Deep phenotyping of patients who developed ChILI, studying their natural history and comparing their characteristics with idiopathic auto-immune hepatitis and DILI due to other drugs. This includes histological characteristics, genetic, biochemical and immunological characteristics.
2. Studying the association between biomarkers, clinical features and development of ChILI.

## **STUDY MANAGEMENT**

Participants enrolled prospectively will be asked to give consent for their samples to be collected, stored and used for the purposes of this study. Clinical and phenotypic data will be collected.

Blood collected will be used for genetic analyses of genetic variants (not genetic testing for clinical genetic disease diagnostics) and for immune cell characterisation. The total volume of blood taken for these samples will not exceed 80ml.

We propose to prepare peripheral blood mononuclear cells (PBMCs) for phenotypic analysis such as scRNAseq and immunological cell-type analyses. Plasma and serum will be prepared from blood samples after collection and analysed or stored at -80°C for subsequent analysis of biomarkers, metabolites and other cellular components. We plan assessment of proposed circulating biomarkers including cytokines, microRNAs (miR-122, miR-4270 and miR-4463)[39], total cytokeratin 18 (K18), macrophage colony-stimulating factor receptor (MCSFR) [11], and any others identified in subsequent publications. Some of these molecules may be quantified by specialist laboratories via service agreements. Urine

biomarkers and metabolites will be evaluated and metabolites and microbiome assessed from stool samples.

We will also collect liver biopsy material surplus from clinical care where available only if taken as part of usual patient treatments for their condition. We plan to use **available** liver biopsies, up to 25 of DILI and 50 of AIH, from other HRA-approved research studies, tissue banks and the histopathology archive at NUHT to examine the cellular features of disease and provide phenotypic details of changes within liver tissues that accompany the disease development.

We will also request consent for any residual samples after the study is complete to be transferred to a research tissue bank or stored under the University HTA license and used for future research by other researchers.

In this case, samples will be stored at the NDDC BRU Research Tissue bank (REC. Ref: 19/WA/0288; IRAS 269956) and made available through the access committee. The Chief Investigator has overall responsibility for the study and shall oversee all study management.

The data custodian will be the Chief Investigator. Anonymised data will be shared with researchers at Pfizer where appropriate for analysis of research findings.

## **DURATION OF THE STUDY AND PARTICIPANT INVOLVEMENT**

### **STUDY DURATION:**

Five years.

### **PARTICIPANT DURATION:**

- Checkpoint inhibitors cohort group (part one on diagram): two visits:
  1. Prior starting checkpoint inhibitors
  2. After 6-14 weeks of treatment if no ChILI develops.
- ChILI group (part two on diagram): three visits:
  1. At time of reaction, defined as: *ALT > 5 ULN OR ALT > 3 ULN plus bilirubin > 2 ULN OR alkaline phosphatase (ALP) > 2 ULN* with accompanying elevations of gamma-glutamyl transferase in the absence of known bone metastases driving the rise in ALP level.
  2. One week later (2-14 days after Visit 1).
  3. One month later (30 ± 7 days after the Visit 1).

In cases where ChILI develops in the checkpoint inhibitors cohort group (part one), there will be a total of 4 visit – prior starting CPI, time of reaction, 1 week after reaction and 1 month after reaction

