### Proposal Aims:

1. To establish the incidence of ChILI and other immune-related adverse events over a period of 6-14 weeks following checkpoint inhibitor therapy.
2. To identify and characterise biomarkers associated with the diagnosis of ChILI by comparing biomarkers of patients who developed ChILI with patients who had CPI treatment without developing liver injury with follow up to 14 weeks.

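### The primary incidence of ChILI and other irAEs has no single risk horizon, because scheduled follow-up of a ChILI-free cohort patient ends at one visit held anywhere in weeks 6 to 14

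*Protocol*

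**What the plan says.** Under Proposal Aims, the first aim is "To establish the incidence of ChILI and other immune-related adverse events over a period of 6-14 weeks following checkpoint inhibitor therapy". The second aim describes the comparison group as "patients who had CPI treatment without developing liver injury with follow up to 14 weeks".

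Part 1 of the Study Configuration sets the contact schedule: "Two visits will be undertaken (prior starting CPI therapy and 6-14 weeks after treatment". The same section gives the reason for the timing: "Timing of ChILI ranges from 1 – 49 weeks following treatment with a peak around 6 – 14 weeks".

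Participant Duration gives the second cohort visit as "After 6-14 weeks of treatment if no ChILI develops". A cohort patient who does develop ChILI has four visits in all: baseline and three from the reaction onward. That count leaves no place for a completed week 6-14 visit followed by conversion. End of the Study is the last visit of the last participant, so no later contact is scheduled.

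The Statistical analysis section says only: "We will calculate the incidence of ChILI and other irAE in the cohort group". It names no estimator, time origin or horizon. Incidence is listed first under both Primary endpoint and Primary Outcome Measure.

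**The concern.** An incidence proportion means something only with a period attached. Here the period differs from patient to patient, by up to eight weeks, and the difference falls where the protocol says risk is concentrated. A patient seen at week 6 is closed as ChILI-free when the stated peak is just beginning; one seen at week 14 has passed through it.

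Two sites with the same underlying risk could then report different incidences only because one books Visit 2 earlier. The pooled figure could not be set against a published rate that has a defined period. The same holds for the other immune-related events counted in this outcome.

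There is a secondary consequence. The protocol also wants to relate biomarkers and clinical features to the development of ChILI (Secondary Objectives, Secondary endpoint, Secondary Outcome Measure). In those analyses a patient who develops ChILI after an early Visit 2 would be counted as a non-case.

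**Working it through.** **Stated figures.** The protocol gives no precision or power calculation for the incidence, so there is no figure to reproduce. Its quantitative inputs are: Visit 2 in weeks 6-14; onset in weeks 1-49 with a peak in weeks 6-14; ChILI incidence of 3-18%, with no period attached; and 120 controls.

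**Direction, which needs no distributional assumption.** Let F(t) be the cumulative share of onsets by week t, and v a patient's Visit 2 week. A patient followed to v contributes risk proportional to F(v). F cannot decrease, so F(v) ≤ F(14) for every v ≤ 14. A simple proportion is therefore at or below the 14-week risk, with equality only if no onsets fall between Visit 2 and week 14.

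**Size, which does need assumptions.** The share of the 14-week risk that is captured is the mean of F(v)/F(14) over the visit dates. The protocol gives neither the shape of F nor the spread of visits, so both are assumed. Two examples by hand:

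- Uniform onset over weeks 1-49: F(t) = (t − 1)/48. At week 6: (5/48)/(13/48) = 5/13 = 0.38. With visits even over weeks 6-14 the mean visit is week 10: 9/13 = 0.69.
- 15% of onsets before week 6, 70% in weeks 6-14 and 15% later, uniform within each period: F(6) = 0.15, F(14) = 0.85. At week 6: 0.15/0.85 = 0.18. With even visits: (0.15 + 0.35)/0.85 = 0.59.

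Share of the 14-week risk captured under five shapes:

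| Assumed onset shape | All at week 6 | Even, weeks 6-14 | Even, weeks 10-14 | Even, weeks 12-14 |
|---|---|---|---|---|
| Uniform, weeks 1-49 | 0.38 | 0.69 | 0.85 | 0.92 |
| Triangular, weeks 1-49, mode week 10 | 0.17 | 0.56 | 0.78 | 0.89 |
| 15/70/15% before, in, after weeks 6-14 | 0.18 | 0.59 | 0.79 | 0.90 |
| 20/50/30% | 0.29 | 0.64 | 0.82 | 0.91 |
| 10/85/5% | 0.11 | 0.55 | 0.78 | 0.89 |

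Two gamma shapes with mode at week 10 (shape 3, scale 5; shape 6, scale 2) give 0.61 and 0.55 with visits even over weeks 6-14, inside the same range.

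**In terms of the reported incidence.** Multiply a true 14-week risk I by the captured share r. With visits even over weeks 6-14, a true 3% would read 1.7-2.1% and a true 18% would read 10.0-12.5%.

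**Patients closed as ChILI-free who convert by week 14.** Among 120 such patients the expected number is 120 × I(1 − r)/(1 − I·r). For I = 0.18 and r = 0.69 this is 120 × 0.18 × 0.308/(1 − 0.1246) = 7.6. Across the five shapes, with even visits, it runs from 1.1-1.6 at I = 3% to 7.6-10.7 at I = 18%.

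**The case against.** **The estimator is open.** The protocol does not say that incidence will be a crude count, and an SAP may specify person-time, Kaplan-Meier or Aalen-Johansen with censoring at Visit 2. If visit timing is unrelated to risk, such an estimator removes the shortfall shown above. This stands, and the 55-69% applies only to a simple proportion. But an SAP cannot recover events after an early Visit 2 if no one is asked to look for them, and it would still have to supply a horizon that the aims leave as a range.

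**Low compared with what?** A reader might infer that the estimate is simply biased low. The documents do not support that without a target: it is low against a horizon of 14 weeks or more, not against a 6-week risk. The missing target is the defect.

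**Is there a contradiction in the aims?** A reader might take "without developing liver injury with follow up to 14 weeks" as a promise that every control is followed through week 14. It can equally mean up to 14 weeks, which agrees with the visit window. It is ambiguous, not a proven conflict.

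**Are the controls contaminated?** A reader might conclude that the Part 3 control group is invalid because it contains future cases. That does not hold for the main comparison. Part 3 is cross-sectional and the second primary outcome concerns diagnosis; a patient free of injury when sampled is a valid control for that question, whatever happens later. Even if 5% of controls were indistinguishable from cases, an illustrative AUC of 0.80 would move only to 0.95 × 0.80 + 0.05 × 0.50 = 0.785. The misclassification matters for prediction or development of ChILI, and only there.

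**Late converters are not excluded in principle.** The Control Group section classes cohort patients who develop ChILI as cases, without a time limit. This stands as intent, but no scheduled contact would identify those who convert after Visit 2.

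**Conclusion.** The concern holds as a missing horizon. The first primary outcome is defined over a range of weeks, and scheduled ascertainment of a ChILI-free patient stops at a variable point within the stated peak of onset. As written, a simple proportion would depend on visit scheduling and could not exceed the 14-week risk.

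The existence and direction of the problem rest on the protocol's text alone. Its size does not. The 55-69% capture assumes visits spread evenly over weeks 6-14 and onset shapes that the protocol does not give; it rises to about 78-85% for visits in weeks 10-14 and 89-92% for weeks 12-14. The diagnostic case-control comparison is not undermined. Because the outcome is primary and the correction is cheap, it should be made before incidence is analysed.

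**What to change.** Align Proposal Aims, Participant Duration and Statistical analysis on the following:

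1. **One horizon.** For example, cumulative incidence of ChILI, and of other irAEs, by week 14 from first CPI dose.
2. **Ascertainment to that horizon.** Take each cohort patient's status to week 14 from routine liver tests and clinical records, whatever the date of Visit 2. Visit 2 remains a sampling visit.
3. **Estimator.** Use a time-to-event estimate (Aalen-Johansen) with death before the event as a competing event and censoring at last ascertainment.
4. **Converters after Visit 2.** A patient who develops ChILI after Visit 2 but by the horizon counts in the incidence numerator.
5. **Part 3.** For the cross-sectional diagnostic comparison, a patient free of ChILI when sampled may stay a control. For analyses of prediction or development of ChILI, do not count converters known by the horizon as non-cases; this can be a sensitivity analysis.
6. **Reporting.** State that onsets after week 14 remain unobserved, since the protocol cites onset as late as week 49. A 14-week rule defines the incidence; it does not clear later cases from the controls.

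The cost is revised wording and a records look-up for patients sampled before week 14. The look-up itself needs no added study visit. Its limitation is that converters found this way may have no sample from the time of reaction, so they would count towards incidence but might not be usable as Part 3 cases.
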